### Identification of eligible patients

Patients referred to a renal vascular clinic in an academic health sciences center will be eligible to enter the study. This clinic is devoted to the diagnosis and management of renal vascular disease. After referral, patients have a minimum data set of screening laboratory and diagnostic tests and screening diagnostic tests including a renal ultrasound, Doppler of the renal arteries and RRI. At the baseline visit after collecting appropriate history physical examination and lab data to document the risk factors signs and symptoms of ARVD all the tests are reviewed. If the patient has an intermediate or high probability for revascularization based on a clinical assessment of the history, physical, lab and screening tests, an MR angiogram or CT angiogram is arranged. All patients receive aggressive medical management aimed at cardiovascular and renal risk reduction with a focus on blood pressure and lipid control and use of (Acetyl-salicylic acid) ASA. In this protocol, patients assessed at the baseline visit who are diagnosed with ARVD will be asked to consent to this study. Randomization to revascularization or medical management will take place later for those patients that develop indications for revascularization. All patients with renal vascular disease are followed at three month intervals. Following revascularization, patients are seen monthly for six months. Patients enrolled in the study will be receiving appropriate medical care according to clinical practice guidelines and will be considered part of regular clinical practice. No additional tests or procedures other than the consent to participate in a study, will be performed on those participating in this study.

### Randomization and study blinding

Following informed consent patients found to have renal artery stenosis will be randomized in a permuted block design with blocks of 2 and 4. The randomization schedule has been developed and will be administered by the Biomedical Design and Statistics unit. The randomization code will be kept in a sealed opaque envelope and will not be opened until the patient has an indication for revascularization or the study end is reached. The study investigators, coordinators and patients and all members of the research team will be aware of the randomization when opened but will be blinded to the results of the renal resistance index. The allocation will be administered by study nurse in sealed sequentially numbered envelopes. The study nurse will open the next number in sequence when a randomization has occurred. The date and time of randomization will be recorded and the opened randomization envelope will be filed in the trial centre binder.

### Primary outcome

The primary objective of the RAVE study is to determine the frequency of progression to the composite endpoint, death or dialysis or doubling of creatinine, in patients with ARVD stratified by the renal resistance index. Patients with an indication for revascularization will be openly randomized to medical therapy alone or to renal revascularization as well as medical therapy.

Following revascularization patients will be assessed monthly for 6 months and then every three months. All patients will have at least 6 months of follow-up. The blood pressure and creatinine level at the final visit will be used for the analysis. If an outcome is reached during the study, patients will continue to be followed, but data for the main outcome measure will be based on only the first endpoint reached. Outcomes will be analyzed on an intent-to-treat basis.

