### Diagnosis of ARVD

Early diagnosis and treatment of ARVD may help to improve hypertension and prevent renal impairment. The current diagnostic recommendations from the Canadian Hypertension Education Program clinical practice guidelines can be found in Table 1. Clinically, signs of renal artery stenosis include; abdominal bruit, resistant hypertension requiring three or more anti-hypertensive medications, accelerated or suddenly uncontrolled hypertension and atherosclerosis in other vascular beds. Stenoses less than 50% are not associated with renal impairment or hypertension[11], but those greater than 50% can cause both[7]. Early onset of hypertension before the age of 30 suggests fibromuscular dysplasia, an as yet idiopathic form of renal artery disease and not the subject of this study. Sudden onset of resistant hypertension after the age of 55 years suggests ARVD as does differences in the size of both kidneys greater than 1 cm, on ultrasound. These clinical signs can help identify a patient with increased likelihood of disease. Once ARVD is suspected, a screening test should be performed to confirm its presence. One of the greatest challenges in managing ARVD is that there is no single screening test with sufficient sensitivity and specificity to confidently identify patients who will benefit from revascularization. For example while renal angiography can identify whether there is macrovascular renal artery disease which is amenable to percutaneous transluminal renal angioplasty (PTRA) with or without a stent, it can not determine if the lesion is responsible for the clinical picture or predict whether revascularization will improve blood pressure control or preserve renal function. Angiographic procedures may cause renal harm by introducing contrast dye directly into the kidney as well as introducing athero-emboli by disrupting atheroma along the vessel wall[12]. While revascularization studies have demonstrated good anatomical correction of renal vascular lesions, particularly with renal stenting (which costs many thousands of dollars)[13], even meta analyses of studies of clinical revascularization have shown no improvement in renal function compared to conservative strategies and modest if any improvement in blood pressure control[8]. In general, studies of PTRA without or with stenting (PTRAS) for ARVD have shown that renal function is improved in about 25%, stabilizes in about 40%, but worsens in about 25% of patients[14].

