### Study interventions

The intervention is assignment to a group receiving medical therapy alone. The standard of care currently for patients with renal artery stenosis and an indication for revascularization is to have revascularization. Medical therapy includes aggressive blood pressure lowering to target (< 140/90 mm Hg and < 130/80 mm Hg for those with diabetes), LDL reduction < 2.0 with statin therapy, use of ASA or other antiplatelet therapy, diabetes control, diet, exercise and smoking cessation. Referral for diabetes education and management if appropriate.

Percuateneous transluminal renal angioplasty, involves percutaneous access to the arterial circulation using the Seldinger technique at the level of the femoral artery and the passing of an angiographic wire into the renal artery and proximal aorta for contrast dye injection. Patients are admitted to the nephrology ward the day of the procedure and are discharged the following day after lab work has been completed and reviewed. Antihypertensives are given at half dose on the day of the procedure to prevent symptomatic hypotension. ASA is held the day of the procedure. For those on coumadin, it is held 5 days before and vitamin K 1 mg administered and a normal INR is required prior to the procedure. Stenting will be performed at the discretion of the angiographer. Angioplasty of the renal artery with stenting leads to lower restenosis rates and longer term patency [27]. While it seems logical that this greater patency would lead to improved blood pressure control and preservation of renal function, no study has yet been conducted to prove this.

The choice of balloon size, angiographic method and need for stent will be determined on a case by case basis by the angiographer. In general stents are used for those patients with ostial lesions. Renal revascularization to date has not demonstrated in most patients in blood pressure control and has shown no benefit in renal preservation. The DRASTIC study, the largest study to investigate the effectiveness of a revascularization strategy for ARVD had to screen over 1200 patients referred with resistant hypertension to find 543 who received angiography for diastolic blood pressure ≥ 95 mm Hg. Of these, 169 (30%) were found to have renal artery lesions ≥ 50% [28]. The DRASTIC study did not use renal stenting and did not preselect patients using the RRI. Patients that require surgical revascularization will be withdrawn from the study.

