### Patient follow-up procedures

Any patient randomized to medical therapy who has an indication for revascularization will have attempted further medical management for another 3 months. Patients randomized to revascularization who have an indication will be offered revascularization. All patients will be followed prospectively for both an intent to treat and per protocol analysis. The analysis will also be carried out stratified by the result of the renal resistance index (normal vs abnormal) to determine it's prognostic ability.

The decision to proceed toward revascularization will be based on a rise in creatinine by > 20% per year from baseline for year one and in year 2, by > 20% over the average creatinine from year one. To reduce the possibility that the rise in creatinine is temporary, due for example to a hypovolemic event, a repeat creatinine will be required from 3 days to 3 months later to confirm that the creatinine has risen by 20%. If an ACEi or ARB has been started after enrollment into the study, a rise in creatinine of 20% in the first 3 months after the initiation will be permitted. The creatinine trigger for revascularization after ACEi or ARB is started will be a creatinine rise of 40% during that year. The blood pressure trigger for revascularization will be systolic blood pressure ≥ 150 mmHg and/or diastolic blood pressure ≥ 95 mmHg on any visit.

Patients randomized to the medical management group will not be excluded from revascularization. If blood pressure is ≥ 170 mm Hg and/or diastolic blood pressure ≥ 100 mm Hg on any visit despite treatment with at least three antihypertensives at maximal dosage patients can be referred for revascularization. In this circumstance, patients will continue to be assessed in an intent-to-treat analysis. If the creatinine doubles from baseline patients can be referred for revascularization.

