### Study withdrawal

Patients will be censored and withdrawn from follow-up at their request. Patients will be censored at the time they reach an endpoint including the need for renal replacement therapy, death or doubling of the creatinine from baseline.

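### The creatinine rise that triggers revascularization must be confirmed by a repeat, but the doubling in the primary endpoint need not be, and the Primary outcome section gives two conflicting rules for scoring it

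*Protocol article*

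**What the plan says.** All places are in the Protocol article.

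- **Trigger.** Patient follow-up procedures gives the reason for confirmation, "To reduce the possibility that the rise in creatinine is temporary, due for example to a hypovolemic event", and then the rule: "a repeat creatinine will be required from 3 days to 3 months later to confirm that the creatinine has risen by 20" per cent.
- **Endpoint.** Primary outcome defines the "composite endpoint, death or dialysis or doubling of creatinine, in patients with ARVD stratified by the renal resistance index". No repeat or persistence is asked for. Study withdrawal censors patients when they reach an "endpoint including the need for renal replacement therapy, death or doubling of the creatinine from baseline", again without a repeat.
- **Scoring.** Primary outcome says both "The blood pressure and creatinine level at the final visit will be used for the analysis" and that "data for the main outcome measure will be based on only the first endpoint reached". It also keeps patients in follow-up after an endpoint.
- **Procedural harm.** Diagnosis of ARVD states: "Angiographic procedures may cause renal harm by introducing contrast dye directly into the kidney". It names athero-emboli as a second mechanism.
- **Timing of measurements.** Under Study interventions, patients who have the procedure are "discharged the following day after lab work has been completed and reviewed". Identification of eligible patients and Primary outcome set monthly visits for the first half-year after revascularization, against three-monthly visits otherwise. Table 4 lists follow-up creatinine every 3 months and shows no separate schedule after a procedure.

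**The concern.** One biomarker is held to two standards. The article guards the treatment trigger against temporary rises, with a reason and a time window, but does not guard the endpoint. If the first doubling reached is the event, a reversible rise is recorded as progression of renal disease and later recovery does not undo it.

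The exposure is uneven. Only patients who have the procedure receive its contrast load and the laboratory work the next day, and they may also be sampled more often. The likely direction of bias in the composite is against revascularization.

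Two results depend on this. Event frequency by arm is the primary objective, and it is meant to feed the sample size of a multicenter trial. The assessment of the renal resistance index (RRI) against response to revascularization could also be distorted if a transient rise is read as non-response.

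The final-visit sentence adds a separate difficulty. Under it, a rise that resolved would not count, so the same patient can be an event under one rule and not under the other.

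**Working it through.** **1. The two scoring rules side by side.** Take a patient whose creatinine doubles soon after the procedure and returns to baseline by the last visit, with no death or dialysis. First-endpoint rule: event. Final-visit rule: no event. The article does not say which governs. The first-endpoint sentence names the main outcome measure. The final-visit sentence pairs creatinine with blood pressure, which is a secondary outcome, so it may be meant for secondary analyses, but it does not say so. Even if final-visit creatinine defined doubling, it would still be one unconfirmed value.

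**2. Denominators.** Table 5 reproduces: 240 × 0.20 = 48; 48 × 2/3 = 32 with RRI below 80; 48 × 1/3 = 16 with RRI of 80 or more; halved, 16/16 and 8/8. The revascularization arm is therefore 16 + 8 = 24. Statistical analysis gives a smaller goal: 20 patients × 0.20 with an indication = 4 randomized, or about 2 per arm.

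**3. False events from the procedure.** The documents give no rate of transient doubling. Assume 2% to 10% of procedures:

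| Patients in revascularization arm | At 2% | At 10% |
|---|---|---|
| 24 (Table 5) | 0.02 × 24 = 0.48 | 0.10 × 24 = 2.4 |
| 2 (goal of 20) | 0.02 × 2 = 0.04 | 0.10 × 2 = 0.2 |

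With 2 patients, the chance of at least one false event is 1 − 0.98² = 4% to 1 − 0.90² = 19%. One such event would be half the arm.

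**4. Effect of sampling frequency alone.** Let q be the assumed chance of a transient doubling at each creatinine measurement, equal in both arms, and k the number of measurements in the first 6 months. Then P(at least one) = 1 − (1 − q)^k. With q = 1% and 24 per arm:

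| Sampling | k | P | Expected per 24 |
|---|---|---|---|
| Three-monthly | 2 | 1.99% | 0.48 |
| Three-monthly plus day-after value | 3 | 2.97% | 0.71 |
| Monthly | 6 | 5.85% | 1.40 |
| Monthly plus day-after value | 7 | 6.79% | 1.63 |

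If creatinine is drawn at every monthly visit, the ratio to the medical arm is 5.85/1.99 = 2.9 to 6.79/1.99 = 3.4. If Table 4 governs and the day-after laboratory work includes creatinine, it is 2.97/1.99 = 1.5. If Table 4 governs and the day-after work does not count, sampling adds no imbalance.

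**5. Effect of a confirming repeat.** Suppose 10% to 30% of transient rises are still present at the repeat (assumed). At q = 1%, expected false events per 24 become 0.05 to 0.14 with 2 measurements and 0.14 to 0.50 with 6 to 7. Confirmation cuts the count sharply but leaves the ratio of about 3, so a common measurement schedule is needed as well.

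**The case against.** The strongest reply is that nothing in the article says one unconfirmed doubling suffices. It is a condensed article, and endpoint confirmation is often left to a fuller document. That stands as a caution, and a reader who infers that the plan prescribes single-value scoring goes beyond the text. It does not dispose of the point: the first-endpoint and censoring rules both fix the event at first attainment, and the article does find room for the trigger's confirmation rule and its window.

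Other objections also have force:

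- **The thresholds differ.** The confirmed trigger is a 20% rise that leads to an invasive procedure; the endpoint is a 100% rise. A large rise is less easily measurement noise. But the stated reason, that a rise may be temporary, does not depend on its size.
- **The day-after sample is unspecified.** The text says only laboratory work; it names no creatinine and does not make it an outcome measurement.
- **The risk is not confined to one arm.** A reader might infer that the medical arm has none of it. Patient follow-up procedures lets medical-arm patients cross over and keeps them in their assigned arm for the intent-to-treat analysis. It also names hypovolemia, and allows for a rise after starting an ACEi or ARB; neither belongs to one arm.
- **Recovery might be captured.** On the final-visit reading, a resolved rise would not count.

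A reader might also set the false events against the 8% with a creatinine rise of at least 50% cited in Sample size considerations (0.08 × 24 = 1.92) and conclude that artefact could equal the true event count. The documents do not support this. That figure uses a lower threshold, leaves out death and dialysis, and comes from a trial whose patients the article expects to progress less than its own.

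**Conclusion.** The point holds in this form: the doubling component lacks the confirmation that the article applies to its own trigger, and Primary outcome contains two scoring statements that must be reconciled. Under the first-endpoint rule, transient doublings can be counted, and more probably in the revascularization arm. The documents do not show that they will be counted, or that they would fall in that arm alone.

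The size is uncertain: about 0.5 to 2.4 false events among 24 patients, or about 0.04 to 0.2 among 2, all resting on an assumed 2% to 10% per procedure. The contribution of sampling frequency ranges from none to roughly a threefold imbalance, depending on whether creatinine follows the visit schedule or Table 4. For a pilot whose main product is an event frequency for planning a larger trial, the endpoint wording should be settled before outcomes are counted.

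**What to change.** Amend the endpoint definition as follows:

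1. Count a doubling only if a repeat creatinine is still at least twice baseline, and date the event at the first value.
2. Use one confirmation window for both arms, for example the 3 days to 3 months already used for the trigger. The next scheduled visit will not serve, since it is about 1 month away after revascularization and 3 months away otherwise.
3. Do not let a day-after-procedure value alone establish the endpoint.
4. Use the same outcome-creatinine schedule in both arms, and reconcile Table 4 with the monthly visits.
5. State that confirmed, first-reached doubling defines the renal component of the primary endpoint, with final-visit creatinine as a separate analysis.
6. Say in advance how a doubling is classified when its repeat falls after a crossover procedure, because the repeat would then reflect that procedure too.
7. Report unconfirmed rises around the procedure as safety events.

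The cost is a change of wording, slightly fewer counted events and an occasional extra creatinine sample, for instance when doubling is first seen at the last visit. Follow-up already continues after an endpoint, so the repeat can be obtained. No treatment rule changes.

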### Secondary outcome

The secondary objectives are to; 1. Compare blood pressure and medications used in patients randomized to revascularization or medical therapy, 2. determine the sensitivity and specificity of the RRI in identifying the response to renal revascularization, 3. determine baseline factors in people with ARVD that are associated with the indication for revascularization and 4. to follow patients over time for both an intent-to-treat and per protocol analysis of outcomes stratified by their renal resistance index finding.

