## Abstract

**Background:**

It is uncertain whether patients with renal vascular disease will have renal or mortality benefit from re-establishing renal blood flow with renal revascularization procedures. The RAVE study will compare renal revascularization to medical management for people with atherosclerotic renal vascular disease (ARVD) and the indication for revascularization. Patients will be assessed for the standard nephrology research outcomes of progression to doubling of creatinine, need for dialysis, and death, as well as other cardiovascular outcomes. We will also establish whether the use of a new inexpensive, simple and available ultrasound test, the renal resistance index (RRI), can identify patients with renal vascular disease who will not benefit from renal revascularization procedures[1].

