## Methods/Design

### Study aims

The primary objective of the RAVE study is to determine the frequency of progression to the composite endpoint, death, dialysis and doubling of creatinine, in patients with ARVD and an indication for revascularization, randomized to medical therapy or renal revascularization over a minimum of 6 months. The secondary objectives are to compare blood pressure and medications used in patients randomized to revascularization or medical therapy, determine the sensitivity and specificity of the RRI in identifying the response to renal revascularization, to determine baseline factors in people with ARVD that are associated with the indication for revascularization and to follow patients over time for both an intent-to-treat and per protocol analysis of outcomes stratified by their renal resistance index finding.

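### The RRI objective is framed as accuracy and prognosis, although the aim is to find patients who do not benefit from revascularization; no section states that the treatment effect will be compared between RRI strata

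*Protocol article*

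**What the plan says.** **Aim.** The Abstract (Background) says the study will establish whether the RRI "can identify patients with renal vascular disease who will not benefit from renal revascularization procedures". The Discussion has the same aim: to spare some patients testing and procedures that would not help them.

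**Stated RRI measures.** Study aims and Secondary outcome both list, as the second secondary objective, to "determine the sensitivity and specificity of the RRI in identifying the response to renal revascularization". The fourth is to "follow patients over time for both an intent-to-treat and per protocol analysis of outcomes stratified by their renal resistance index finding". Patient follow-up procedures gives the purpose of the stratification: "The analysis will also be carried out stratified by the result of the renal resistance index (normal vs abnormal) to determine it's prognostic ability".

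**Primary objective.** Study aims describes the frequency of the composite in patients "randomized to medical therapy or renal revascularization over a minimum of 6 months". Primary outcome describes it "in patients with ARVD stratified by the renal resistance index", and brings in the randomised comparison only in the next sentence.

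**Layout.** Table 5 (Sample size considerations) expects 48 randomised patients: 16 per arm with RRI <80 and 8 per arm with RRI ≥80. Statistical analysis gives a goal of 20 recruited patients, of whom 20% are expected to develop an indication.

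**The concern.** Failing to benefit is a comparison: the outcome with revascularization against the outcome the same kind of patient would have had on medical therapy. Sensitivity and specificity for response to revascularization are naturally read as computed in revascularized patients. A high RRI that signals a worse course whatever the treatment would then appear to predict non-response, even if revascularization worked equally well, or not at all, at every RRI level. Calling the stratified analysis prognostic does not repair this, because prognosis is also not a statement about treatment effect.

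Two things are at stake. First, the section on the renal resistance index reports outcomes by RRI after revascularization and says that the test has not been studied in a randomised prospective trial. An accuracy analysis in the treated arm would repeat that uncontrolled comparison and leave the randomised control group unused for this question. Second, the pilot is meant to support planning of a multicentre trial. If the RRI question is framed as accuracy here, the larger trial may be sized and analysed for the wrong quantity.

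**Working it through.** **1. Table 5 reproduces.** 240 × 0.20 = 48 with an indication. 48 × 2/3 = 32 with RRI <80 and 48 × 1/3 = 16 with RRI ≥80. Halved by arm, this gives 16/16 and 8/8. The article states no significance level, power or effect size, so there is no power figure to reproduce.

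**2. Accuracy when treatment has no effect.** Assume event risks of 40% (RRI ≥80) and 10% (RRI <80) in both arms, and count RRI ≥80 as the positive test for an event. Among the 8 + 16 revascularized patients:
- Sensitivity = 8 × 0.4 / (8 × 0.4 + 16 × 0.1) = 3.2/4.8 = 67%.
- Specificity = 16 × 0.9 / (16 × 0.9 + 8 × 0.6) = 14.4/19.2 = 75%.
- Odds ratio = (0.4/0.6)/(0.1/0.9) = 6.
- Risk difference between arms = 0 in each stratum, so the RRI-by-treatment difference is 0.

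**3. The same accuracy under four different truths.** The section on the renal resistance index cites dialysis rates after revascularization of 46% (RRI ≥80) and 3% (RRI <80). Using these for the revascularized arm:
- Sensitivity = 3.68/(3.68 + 0.48) = 88%.
- Specificity = 15.52/(15.52 + 4.32) = 78%.

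The medical-arm risks below are assumptions. Risk differences (RD) are revascularization minus medical therapy, in percentage points.

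| Medical-arm risk, RRI ≥80 / <80 | Sensitivity / specificity | RD, RRI ≥80 | RD, RRI <80 | Difference between strata |
|---|---|---|---|---|
| 46% / 3% (no benefit) | 88% / 78% | 0 | 0 | 0 |
| 80% / 25% (benefit in both) | 88% / 78% | −34 | −22 | −12 |
| 46% / 25% (benefit only at low RRI) | 88% / 78% | 0 | −22 | +22 |
| 80% / 3% (benefit only at high RRI) | 88% / 78% | −34 | 0 | −34 |

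The accuracy columns never change. In the last row the RRI ≥80 patients are the only ones who benefit, yet accuracy would mark them as the non-responders.

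**4. Precision of the contrast that does answer the question.** The standard error of the difference between the two risk differences, with the 40%/10% risks in both arms, is √(2 × 0.24/8 + 2 × 0.09/16) = √0.07125 = 0.267. The 95% half-width is 1.96 × 0.267 = 0.52, or 52 points. For the third row of the table it is 54 points. With a two-sided 5% level (assumed), power to detect that 22-point difference would be 13%, and about 589 randomised patients would be needed for 80%.

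**5. Under the 20-patient goal.** 20 × 0.20 = 4 randomised. The expected numbers per arm are 4 × 1/3 ÷ 2 = 0.67 at RRI ≥80 and 4 × 2/3 ÷ 2 = 1.33 at RRI <80. The chance that all four arm-by-RRI cells hold a patient is 4! × (1/6)² × (1/3)² = 7% if allocation is independent. If blocking gives exactly two per arm, it is (2 × 1/3 × 2/3)² = 20%. Even then each cell holds one patient and gives no usable variance.

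**The case against.** The strongest reply is that the randomised comparison within RRI strata is already there. Objective 4 is an intent-to-treat and per-protocol analysis by RRI, and both terms refer to randomised arms. Table 5 sets the arms out inside each stratum. In Patient follow-up procedures, the stratification sentence directly follows the one announcing those two analyses. A reader might infer from objective 2 and the prognostic wording that the control group is ignored and that no randomised contrast by RRI is planned. The documents do not support that, and this part of the objection stands.

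It is also fair that an interaction term, its scale and its interval are commonly left to an analysis plan or a full protocol, neither of which is shown. Their absence from an article would be no finding. The point is narrower: the article does fix a measure, twice, and does fix the purpose of the stratification as prognostic. Neither matches the aim, and an analysis plan that followed those objectives faithfully could report accuracy as the answer.

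Three further points have weight:
- The denominator for sensitivity and specificity is not stated, so restriction to revascularized patients is the natural reading and not a stated fact. If both arms were pooled, the measure would still describe prognosis.
- The Discussion is conditional throughout and does not commit the pilot to a rule for withholding the procedure. A reader might infer such a commitment, but the text does not make one.
- The pilot cannot test the contrast at either sample size. That argues against a test, not against naming the right quantity, and accuracy estimates from so few patients are weak too.

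**Conclusion.** The mismatch between the aim and the stated RRI measures is real and should be corrected, but it concerns framing and does not mean that the analysis is absent. The trial will hold the data for the right contrast; what is missing is a statement that the treatment effect will be compared between RRI strata. As worded, objective 2 could return 67% sensitivity and 75% specificity when revascularization has no effect in either stratum, or 88% and 78% under four incompatible patterns of benefit.

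These figures rest on Table 5's cell sizes, on accuracy being computed among revascularized patients, and on an event standing in for non-response. The 40%/10% risks and all medical-arm risks are illustrative assumptions. The 46% and 3% are cited dialysis rates, not rates of the trial's composite. That treated-arm accuracy says nothing about benefit does not depend on the particular values.

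**What to change.** Either within objective 4 or in place of objective 2, state the RRI estimand as follows: the difference in risk of the composite (revascularization minus medical therapy) among all randomised patients by intent-to-treat, within RRI <80 and within RRI ≥80, and the difference between those two risk differences, each with a 95% confidence interval. Label it a pilot estimate, not a test. Amend the purpose given in Patient follow-up procedures to match.

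Keep sensitivity and specificity only as a descriptive prognostic summary, shown side by side for both arms, with a sentence saying that they do not measure benefit.

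The change costs wording only; the data are the same. The drawback is a visibly imprecise result: about ±52 points at 48 randomised under the assumed risks, and possibly no estimate at all if the 20-patient goal yields about 4. The text should say so, and say that in that case the four cell counts will be reported without the contrast.
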